**Discussion:**

This study will reveal the usefulness of ESPB and QLB in terms of postoperative analgesic efficacy and safety in patients undergoing laparoscopic liver resection. Additionally, the study results will provide information on the analgesic superiority of ESPB versus QLB in the same population.

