### Outcomes {12}

The primary outcome is cumulative opioid consumption 24 h after surgery. Secondary outcomes include: cumulative opioid consumption in the PACU (admission, highest, and discharge), at 48 h, and 72 h after surgery; pain severity at rest and when coughing in the PACU (admission, highest, and discharge), at 24 h, 48 h, and 72 h after surgery; postoperative nausea or vomiting in the PACU, at 24 h, 48 h, and 72 h after surgery; quality of sleep on the first night; patient satisfaction with pain relief at 24 h after surgery; postoperative recovery quality at 24 h after surgery using the Korean version of the Quality of Recovery-15 scale (QoR-15 K) [11]; the incidence of procedure-related complications (hematoma, infection, or needle trauma); time to first flatus; and plasma ropivacaine concentrations at 30 min, 45 min, 60 min, and 240 min after the end of both administrations of local anesthetics.

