## Assignment of interventions: allocation

### Sequence generation {16a}

Eligible participants will be randomly assigned to the control, ESPB, or QLB group in a 1:1:1 ratio. Randomly assigned sequences are generated using a web-based service (www.sealedenvelope.com) by an independent statistician with a fixed block size of six.

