## Statistical methods

### Statistical methods for primary and secondary outcomes {20a}

After assessing normality, continuous variables will be presented as mean ± standard deviation or median with an interquartile range. Categorical variables will be presented as numbers (%).

The primary outcome, cumulative opioid consumption 24 h after surgery, will be compared using Dunnett's test. For continuous variables of the secondary outcomes, descriptive statistics for each group will be presented, and the mean difference among the groups will be confirmed using one-way analysis of variance (ANOVA). If the assumption of normality is not satisfied, the median difference among the groups will be analyzed using the Kruskal–Wallis test. For plasma ropivacaine concentration, the peak plasma ropivacaine concentration (Cmax) and time to Cmax (Tmax) will be compared using an independent two-sample *t*-test or Wilcoxon rank-sum test, depending on normality testing. For categorical variables, the difference in the ratio among the three groups will be confirmed using the chi-square test or Fisher’s exact test. Statistical significance shall be set at a two-sided *P* < 0.05. The analysis will be performed using SPSS, Version 27.0 (IBM Corp, Armonk, NY, USA).

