Our study has several limitations. First, the sham procedure is not used for participants in the control group. Second, the optimal dose of ropivacaine for ESPB or QLB has not been determined. Because ropivacaine is mainly eliminated by hepatic metabolism, delayed ropivacaine clearance in patients with liver disease may increase the risk of local anesthetic systemic toxicity (LAST), which may be aggravated after liver resection [26]. Based on our previous study [10], the peak plasma concentrations of ropivacaine were approximately 3-fold below the threshold for systemic toxicity after administration of 40 mL of 0.375% ropivacaine. Therefore, the 40 mL of 0.5% ropivacaine (approximately 15% increased dose) used in this study is not expected to reach the systemic toxicity threshold. Third, to ensure safety, only 20 participants from each block group will be tested for plasma ropivacaine concentration. The sample size of 20 may be too small to discriminate LAST between the groups. Fourth, we plan to measure total plasma ropivacaine concentrations. However, ropivacaine toxicity is dependent on unbound ropivacaine clearance, and the total plasma ropivacaine concentration alone may not be sufficient to determine systemic toxicity [27].

In summary, we anticipate that this trial will provide evidence for the efficacy and safety of ESPB and posterior QLB in patients undergoing laparoscopic liver resection. In addition, our data will provide clinical implications for determining the optimal dose of ropivacaine for ESPB and posterior QLB.

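### Block-related complications are tested across three groups although the control arm, with no block and no sham, cannot have the event; exact limits per block group would fit the endpoint

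*Protocol article*

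**What the plan says.** Outcomes {12} lists as a secondary outcome "the incidence of procedure-related complications (hematoma, infection, or needle trauma". Objectives {7} includes block-related adverse events up to 72 h among the outcomes to be compared across the groups.

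Statistical methods {20a} has one inferential rule for categorical data: "For categorical variables, the difference in the ratio among the three groups will be confirmed using the chi-square test or Fisher’s exact test". The threshold is P < 0.05: "Statistical significance shall be set at a two-sided". The same section promises counts and percentages. The pairwise methods in the additional-analyses section {20b} (t-test or Wilcoxon, Tukey, Dunn) are for continuous or ranked data, so they offer no alternative for a binary complication.

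Allocation is equal across three arms: "Eligible participants will be randomly assigned to the control, ESPB, or QLB group in a 1:1:1 ratio". Under Intervention description {11a} only the ESPB and QLB groups receive a block, and the limitations in the Discussion state that "the sham procedure is not used for participants in the control group".

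On the aim, the Abstract says: "This study will reveal the usefulness of ESPB and QLB in terms of postoperative analgesic efficacy and safety in patients undergoing laparoscopic liver resection". The closing summary says: "we anticipate that this trial will provide evidence for the efficacy and safety of ESPB and posterior QLB".

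**The concern.** The rule suits nausea or vomiting, which can occur in all three arms. It does not suit a complication of the block itself, for two reasons.

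- **The control arm is a structural zero.** Equal proportions in all three groups can hold only if both blocks have a complication rate of exactly zero. The control patients add to the table but carry no information on how often a block causes harm.
- **The trial is sized for opioid consumption.** With 34 to 38 patients per arm, the test will usually be non-significant even at complication rates that would matter.

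At stake is what the report can say about needle-related harm. A P value from this table is close to uninformative. The same counts can support an upper limit on each block's complication rate, which the stated method does not provide.

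**Working it through.** **Arm size, from the protocol's own figures.** Sample size {14} gives 34 per group and 10% dropout: 34 / 0.9 = 37.8, rounded up to 38, and 3 × 38 = 114, which agrees with the planned enrolment. So n = 38 per arm if everyone is analysed and n = 34 if the expected dropouts occur.

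**Other inputs.** Two-sided alpha 0.05 ({20a}). Control rate 0, since controls have no block ({11a}) and no sham (Discussion). The documents give no complication rate for the blocks, so 5% and 10% are assumed as a range.

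**Miss probability.** With 0 events in control and b, c events in the two block arms, each binomial with n patients and rates p1 and p2:

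Miss = 1 − Σ over (b, c) of Bin(b; n, p1) × Bin(c; n, p2) × I[P(0, b, c) < 0.05]

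P is either the exact Fisher-Freeman-Halton P value for the 3 × 2 table or the uncorrected chi-square P value on 2 df. All outcomes were enumerated.

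| True rates in the two blocks (control 0%) | n per arm | Fisher misses | Chi-square misses |
|---|---|---|---|
| 5% and 5% | 38 | 93.0% | 88.1% |
| 10% and 10% | 38 | 62.0% | 63.6% |
| 5% and 10% | 38 | 71.2% | 68.3% |
| 0% and 5% | 38 | 88.0% | 70.4% |
| 0% and 10% | 38 | 46.5% | 25.4% |
| 5% and 5% | 34 | 94.6% | 89.3% |
| 10% and 10% | 34 | 71.4% | 71.9% |

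**Example by hand, 0/4/4 events at 38 per arm** (4/38 = 10.5% in each block):

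- Expected events per arm are 8/3 = 2.667; expected non-events are 106/3 = 35.333.
- Squared deviations: 2.667² + 2 × 1.333² = 10.667.
- Chi-square = 10.667/2.667 + 10.667/35.333 = 4.000 + 0.302 = 4.302.
- On 2 df, P = exp(−4.302/2) = 0.116. Fisher gives P = 0.124.

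Five events in each block (13.2%) bring Fisher to P = 0.045, while chi-square is still at 0.065.

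**What the counts can support.** With zero events, the exact (Clopper-Pearson) two-sided 95% upper limit is 1 − 0.025^(1/n):

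- 0/38: 1 − 0.025^(1/38) = 9.3%
- 0/34: 1 − 0.025^(1/34) = 10.3%
- 1/38, from the beta quantile: 13.8%

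**ESPB against QLB.** With 38 per arm and true rates of 5% and 10%, a two-group Fisher test misses the difference 96% of the time. That contrast should therefore also be read as an interval, and the interval will be wide.

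**The case against.** Several points on the other side are sound.

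- **Other safety evidence is planned.** A reader might infer that the complication test is the only inferential support for the promised safety evidence. It is not. The Introduction ties plasma ropivacaine to the safety of the dose, {20a} plans a formal comparison of Cmax and Tmax between the blocks, and opioid-related adverse events are collected. The accurate statement is narrower: this is the only inferential analysis of block complications. The Cmax and Tmax comparison sets one block against the other and does not bound the complication rate.
- **No inference from non-significance is stated.** A reader might infer that the plan will treat P > 0.05 as evidence of safety. No passage says so, and the Discussion concedes that 20 patients per block group may be too few to discriminate systemic toxicity. The misreading is a foreseeable risk, not something the protocol commits to.
- **The miss rates are conditional.** They rest on assumed rates, and they are much lower if only one block carries the risk.
- **Low power for rare harms is ordinary** in a trial of this size, and neither the primary analysis nor any efficacy conclusion is affected. Counts and percentages will be reported, so a reader could derive an exact limit.
- **Interval methods often sit in an analysis plan that is not shown.** A missing interval alone would not be a finding. Here, however, the article states a method, and Objectives {7} confirms that the comparison among groups is meant to cover this endpoint. The stated method does not fit an event that one arm cannot have.

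The denominator also matters. Section {11b} counts patients with inappropriate local anesthetic spread or unexpected serious adverse events as dropouts. They could disappear from the complication count unless the analysis set is stated.

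**Conclusion.** The point holds in its narrow form. The only inferential analysis stated for block-related complications is a three-group test that includes an arm where the event cannot occur, and that test has little power. Assuming 38 analysed per arm, control 0% and equal rates in both blocks, Fisher misses a 5% rate 93% of the time and a 10% rate 62% of the time. Chi-square misses 88% and 64%, and Fisher at 34 per arm misses 95% and 71%. If only one block carries a 10% rate, at 38 per arm the miss rate falls to 46.5% with Fisher and 25.4% with chi-square.

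The structural-zero argument does not depend on the assumed rates; the miss rates do. It rests on reading the complications as those of the block procedure, as the block-related wording in the Abstract and Objectives indicates. The consequence is confined to what may be said about needle-related complications. A reader might want to limit the whole safety statement to what a 9% bound excludes, but that would go too far, because the statement also covers the plasma ropivacaine work.

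**What to change.** In Statistical methods {20a}, take block-related complications out of the three-group chi-square/Fisher rule and state:

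- They will be summarised separately in the ESPB and QLB groups, among all patients in whom a block was attempted, including those that {11b} counts as dropouts, as far as their consent allows.
- Each group will be reported as number, percentage and exact (Clopper-Pearson) 95% confidence interval, with the upper limit given even if no event occurs.
- The ESPB-QLB difference will be given with an exact 95% confidence interval.

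In the Abstract and the closing summary, limit any statement about needle-related complications to what the upper limit excludes (with no events, rates above 9.3% for 0/38 or 10.3% for 0/34). The plasma ropivacaine statements need no change.

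The cost is a few sentences of analysis wording and one table column, with no extra patients; complications must also be recorded for patients counted as dropouts. The downside is that an upper limit near 9% or 10% reads less favourably than a report of no significant difference.

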### Interim analyses {21b}

Not applicable. An interim analysis is not planned for this trial.

### Methods for additional analyses (e.g., subgroup analyses) {20b}

Subgroup analyses will be performed for pairwise comparison. We will compare the primary outcome, cumulative opioid consumption at 24 h after surgery, between the two groups in each pair using an independent two-sample *t*-test or Wilcoxon rank-sum test as appropriate. Multiple comparisons for subgroup analysis will be adjusted using Bonferroni correction. One-way analysis of variance (ANOVA) with Tukey’s test will be used to perform pairwise comparisons for other outcomes. If the data do not satisfy normality, the Kruskal–Wallis test and Dunn’s method will be used to perform multiple comparisons.

### Methods in analysis to handle protocol non-adherence and any statistical methods to handle missing data {20c}

There will be no non-adherence issues in this study because the institutional standard protocol for postoperative pain management will be provided to all participants. The possibility of missing values in the primary outcome will be very low because data on opioid consumption will be collected using electronic medical records and PCA logs. Missing data will not be replaced.

### Plans to give access to the full protocol, participant-level data, and statistical code {31c}

Sharing participant-level dataset data can be considered by the corresponding author upon reasonable request.

## Oversight and monitoring

### Composition of the coordinating center and trial steering committee {5d}

The coordinating center is the Department of Anesthesiology and Pain Medicine of the Samsung Medical Center, Seoul, Korea. The trial steering committee consists of the chief investigator ([name]) and sub-investigators ([name] and [name]), who are responsible for recruiting patients, conducting the study, and data entry.

### Composition of the data monitoring committee, its role and reporting structure {21a}

The data quality of the trial will be evaluated by an independent data monitoring committee composed of the Samsung Medical Center Institutional Review Board, which is independent of the sponsor and competing interests. Data quality reporting will be conducted by the chief investigator.

### Adverse event reporting and harms {22}

The chief investigator will report any serious adverse events to each institutional review board within seven days of the notice. Mild adverse events and harm will be reported within 15 days of notice. When reporting adverse events or harm, we shall equally report causalities, time of occurrence, severity, seriousness, provided management, and the relationship with the present clinical trial.

### Frequency and plans for auditing trial conduct {23}

The research team will meet for self-auditing trial conduct every month. The trial will be conducted under the supervision of the Samsung Medical Center Institutional Review Board and may be audited at any time by the National Research Foundation of Korea.

### Plans for communicating important protocol amendments to relevant parties (e.g., trial participants, ethical committees) {25}

Any amendments to the protocol will be posted in the trial registry after approval by the Institutional Review Board.

### Dissemination plans {31a}

The results will be disseminated via publication in a peer-reviewed journal and may be presented at medical conferences.

## Discussion

For decades, opioid-based analgesia has been widely used to provide post-operative abdominal analgesia. Despite the excellent postoperative pain control of opioids, concerns have been raised regarding an increase in opioid-related side effects due to impaired metabolism of opioids after liver resection [7, 13]. In this regard, the ERAS protocol for liver resection [4] recommends multimodal analgesia combined with IV opioids as the standard analgesic for perioperative care during liver surgery and the limited use of systemic opioids as rescue analgesics [4, 14]. However, the use of non-opioid analgesics and adjuvant anesthetics is limited by the fixed maximum daily dose and therapeutic ceiling [15]. The regional anesthesia is relatively free from these concerns, compared with systemic analgesics. Accordingly, the latest Procedure-Specific Postoperative pain management (PROSPECT) guidelines for liver resection recommends that alternative analgesic techniques such as local anesthetic infiltration of surgical incisions or interfascial plane block would be helpful after liver resection [14]. However, there is a lack of evidence on what type of interfascial plane block should be performed in laparoscopic liver resection.

In this study, we chose the ESPB and posterior QLB as components of multimodal analgesia for the following reasons. First, both ESPB and QLB have been reported to provide postoperative abdominal analgesia in liver surgeries [10, 16–18]. The mechanism of action of ESPB is that injected local anesthetics spread to the paravertebral space and block the dorsal–ventral rami of the spinal nerve and sympathetic ganglia, providing somatic and visceral analgesia [19]. The mechanism of action of the QLB is that the injected local anesthetic spreads to the thoracoabdominal nerves [20]. Of the three approaches to QLB (anterior, lateral, and posterior), we chose posterior QLB, which provides a widespread sensory block of both somatic and visceral fibers from T7 to L1 or L2 levels [20]. Second, both the ESPB and QLB have been reported to be easy to perform and safe. EPSB is considered a superficial block with a low risk of bleeding or visceral injury because there are no critical structures in close proximity [21]. The QLB is considered a relatively deep fascial block [22], requiring caution, as the branches of the lumbar artery and intra-abdominal viscera are located adjacent to the needle trajectory [20]. However, the posterior QLB is performed in the most superficial plane of the three approaches. The needle tip is separated from the peritoneum by the quadratus lumborum, which acts as a safety barrier to reduce the risk of visceral damage [23]. Complications associated with QLB are considered minor, and no severe permanent complications have been reported [22, 24, 25].

However, evidence for the analgesic effect of ESPB and QLB is still insufficient, and the results are inconsistent in patients undergoing laparoscopic liver resection. Data on the optimal dose of ropivacaine for ESPB or QLB are limited. Our previous study demonstrated the analgesic effect of ESPB with 40 mL of 0.375% ropivacaine in terms of opioid consumption at 24 and 72 h after laparoscopic liver resection in living liver donors [17]. However, another study conducted at our institution reported only limited opioid-sparing effects in PACU stay despite the use of the same dose of local anesthetics in patients undergoing laparoscopic liver resection [5]. For posterior QLB, we could not verify the analgesic effect of QLB compared with ITM in laparoscopic liver resection for living liver donors [18]. Most recently, we conducted a randomized study comparing the analgesic efficacy of ESPB and QLB using 40 mL of 0.375% ropivacaine after laparoscopic liver resection [10]. The results of this study acknowledged the analgesic potential of QLB but did not demonstrate clear differences in opioid consumption at 24 h after surgery. We considered the reasons for these results to be methodological limitations, including the lack of a comparator and low dose of local anesthetics. To address the limitations of the previous study, we set up a control group of systemic analgesics, and a higher dose of ropivacaine (40 mL of 0.5% ropivacaine) will be employed in this study.

Our study has several limitations. First, the sham procedure is not used for participants in the control group. Second, the optimal dose of ropivacaine for ESPB or QLB has not been determined. Because ropivacaine is mainly eliminated by hepatic metabolism, delayed ropivacaine clearance in patients with liver disease may increase the risk of local anesthetic systemic toxicity (LAST), which may be aggravated after liver resection [26]. Based on our previous study [10], the peak plasma concentrations of ropivacaine were approximately 3-fold below the threshold for systemic toxicity after administration of 40 mL of 0.375% ropivacaine. Therefore, the 40 mL of 0.5% ropivacaine (approximately 15% increased dose) used in this study is not expected to reach the systemic toxicity threshold. Third, to ensure safety, only 20 participants from each block group will be tested for plasma ropivacaine concentration. The sample size of 20 may be too small to discriminate LAST between the groups. Fourth, we plan to measure total plasma ropivacaine concentrations. However, ropivacaine toxicity is dependent on unbound ropivacaine clearance, and the total plasma ropivacaine concentration alone may not be sufficient to determine systemic toxicity [27].

In summary, we anticipate that this trial will provide evidence for the efficacy and safety of ESPB and posterior QLB in patients undergoing laparoscopic liver resection. In addition, our data will provide clinical implications for determining the optimal dose of ropivacaine for ESPB and posterior QLB.

## Trial status

The protocol described in this paper is dated July 22, 2022 (version 1.1). The study protocol is registered with the Clinical Research Information Service on 03 August 2022 (KCT0007599). The first participant was recruited for the trial on August 11, 2022, and recruitment is anticipated to be completed on July 31, 2023.

## Data Availability

The dataset generated by the current protocol will be available from the corresponding author upon reasonable request. The study results will be shared with the public through publication in a peer-reviewed journal.

## Abbreviations

ANOVA: Analysis of variance
BIS: Bispectral index
CRF: Case report form
ESPB: Erector spinae plane block
IV: Intravenous
LAST: Local anesthetic systemic toxicity
MED: Morphine equivalent dose
NSAID: Non-steroidal anti-inflammatory drugs
PCA: Patient controlled analgesia
PROSPECT: Procedure-specific postoperative pain management
QLB: Quadratus lumborum block
SD: Standard deviation
